### Outcomes

The primary outcome will be the mean difference in the changes in office SBP from baseline to 12 weeks between TEAS and usual care groups. SBP will be measured as per the WHO STEPS protocol to ensure consistency of recordings, and an automated monitor (HEM-7136, Omron, Kyoto, Japan) will be used at each visit. Patients will be asked to rest quietly for at least 5 min in the sitting position before measuring blood pressure. Blood pressure of both arms will be measured at baseline with the upper arm at heart level, and the arm with higher blood pressure will be the one measured throughout the entire study. At each time point, the blood pressure measurement will be repeated 3 times every 5 min, and the last two will be averaged.^23 24^

Secondary outcomes will include differences in the changes in office DBP between the TEAS and usual care groups; the proportion of patients with well-controlled blood pressure (office blood pressure <140/90 mm Hg); the proportion of patients taking antihypertensive drugs; differences in the changes in number of antihypertensive drugs; and differences in the changes in 12-item Short-Form.^25^ Tertiary outcomes will include change in body mass index; change in waist circumference; physical activity assessed using International Physical Activity Questionnaire^26^; medication adherence assessed using the 8-item Morisky Medication Adherence Scale 8^27^ in patients taking antihypertensive drugs in both groups; and TEAS adherence assessed using number of sessions completed in TEAS group. All secondary outcomes and tertiary outcomes will be measured at weeks 12, 26 and 52. Moreover, blinding test of outcome assessors will be measured at week 12.

Safety outcomes will be any serious adverse events and clinical events (death, myocardial infarction, stroke and cardiovascular-related hospitalisations) at weeks 12, 26 and 52 in both groups. The schedule of enrolment, intervention and assessments is shown in figure 3.

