## Abstract

**Introduction:**

Hypertension is a common risk factor for cardiovascular disease. Transcutaneous electrical acupoint stimulation (TEAS) may be effective for hypertension, but the evidence remains limited. The aim of this study is to evaluate the effectiveness and safety of the smart phone-based TEAS as adjunctive therapy for hypertension.

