**Methods and analysis:**

This study is a 52-week cluster randomised controlled trial with 1600 hypertension patients in 32 community health service centres. Patients who meet the inclusion criteria will be randomised into usual care group or TEAS group in a 1:1 ratio. All patients will be provided with usual care as recommended by the guidelines. In addition to this, patients in the TEAS group will receive non-invasive acupoint electrical stimulation for 30 min at home, 4 times weekly for 12 weeks. The primary outcome will be the mean difference in the changes in office systolic blood pressure from baseline to 12 weeks between TEAS and usual care groups. Secondary outcomes will include the change of mean diastolic blood pressure, proportion of patients with controlled blood pressure (blood pressure <140/90 mm Hg), proportion of patients taking antihypertensive drugs, change in number of antihypertensive drugs and changes in 12-item Short-Form. Tertiary outcomes will include change in body mass index, change in waist circumference, physical activity and medication adherence. Safety outcomes will be any serious adverse events and clinical events.

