## Introduction

Cardiovascular disease is the most common cause of premature death and disability worldwide, and hypertension is the most common risk factor for cardiovascular disease.^1^ WHO suggested that the global prevalence of hypertension was 20% for females and 25% for males.^2^ Moreover, according to the latest American College of Cardiology/American Heart Association guideline,^3^ the prevalence of hypertension increased to nearly 50%.^4–6^ Hypertension accounted for 9.4 million deaths and 7.0% of global disability-adjusted life-years.^7^ The total costs of hypertension will increase to an estimated US$274 billion by 2030.^8^

Lifestyle modifications are recommended by all guidelines in different countries,^3 9 10^ while most patients are unable to sustain lifestyle changes. Antihypertensive drugs are widely prescribed for patients with hypertension. However, fewer than 20% of patients with hypertension have their blood pressure controlled.^10^ The reasons for low control rate of blood pressure include the poor adherence of medicine and the burden of logistics. Identifying non-pharmaceutical therapy with good adherence that can be done at home is urgently needed to reduce blood pressure in patients with hypertension.

Acupuncture, as a non-pharmaceutical therapy, was used for several cardiovascular diseases.^11 12^ Previous studies indicated that acupuncture could decrease blood pressure^13 14^ and a recent systematic review found that acupuncture as adjunctive therapy may be effective for hypertension.^15^ However, acupuncture also has the same limitation of logistical burdens as the antihypertensive drugs. Transcutaneous electrical acupoint stimulation (TEAS), a non-invasive acupuncture therapy, has a similar effect with acupuncture^16–18^ and can be performed at home by the patients themselves. Our pilot study found that TEAS added to usual care for patients with hypertension was feasible and may be a potential treatment option.^19^ The aim of this cluster randomised controlled trial is to evaluate the effectiveness and safety of the smart phone-based TEAS as adjunctive therapy for hypertension.

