#### Exclusion criteria

Other diseases that can affect the blood pressure, including but not limited to diseases of renal parenchyma, renal artery stenosis, obstructive sleep apnoea syndrome, and primary hyperaldosteronism.Receiving medicines that affect blood pressure except antihypertensive drugs in last month, including but not limited to glucocorticoids and central nervous system inhibitors.Contraindications for the use of acupoint stimulators: wearing a pacemaker and other implanted medical devices; epilepsy; scars, bruises, scratches or inflammation on the skin of the acupoints; allergic to electrodes.Uncontrolled diabetes (HbA1c≥6.5%).Drug or alcohol abuse.Pregnant or breast feeding.Participated in other clinical trials in the past 3 months.

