#### TEAS group

In addition to the usual care, the patients in the TEAS group will receive 48 sessions of TEAS treatment (4 times weekly for 12 weeks). TEAS will be performed using a portable instrument (SDP-310, Hwato, Suzhou Medical Appliances, Suzhou, China) with a pair of rounded electrodes (diameter=38 mm) through smart phone. The adhesive electrodes will be applied to the skin as illustrated in figure 2 after the skin sites are cleaned with alcohol to avoid any barrier conduction of the electrical current. The instrument has ten levels of stimulus intensities, and patients asked to increase the stimulus intensity until local, rhythmic contractions of the muscle are obtained without producing pain. According to the previous studies,^16 19 21 22^ bilateral *Hegu* (LI4), *Quchi* (LI11), *Zusanli* (ST36) and *Taichong* (LR3) will be used in our trial. On the first day, the electrodes will be placed at the ipsilateral LI4 and LI11, and the appropriate stimulus intensity will last for 15 min. Then the opposite arm will be stimulated in the same way for another 15 min. On the third day, the ST36 and LR3 will be stimulated for 15 min per leg in the same way. Two pairs of acupoints (LI4-LI11 and ST36-LR3) will be stimulated alternatively every other day. Locations of acupoints are shown in table 1. The acupuncturists will train the patients on how to locate the acupoints and use the instrument face to face. Instructions and acupoint maps will also be provided to help patients to locate the acupoints at home. The patients will be told that the acupoints stimulation can be done when they are leisure at home, like reading the newspaper or watching television. The date, duration and specific acupoints of each acupoint stimuli will be recorded real timely by TEAS software. Thus, the investigator could recognise patients with poor compliance in a timely manner and prompt them to complete the predefined 48 sessions.

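### The listed safety outcomes stop at serious and major clinical events, so the safety aim is only partly covered: serious harm is addressed, local tolerability of the home device is not

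*Protocol article*

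**What the plan says.** The Abstract and the Introduction of the protocol article both give a double aim. The Introduction words it as "to evaluate the effectiveness and safety of the smart phone-based TEAS as adjunctive therapy for hypertension".

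The Outcomes section then defines the safety outcomes: "Safety outcomes will be any serious adverse events and clinical events (death, myocardial infarction, stroke and cardiovascular-related hospitalisations"). They are assessed at weeks 12, 26 and 52 in both groups. The Abstract (Methods and analysis) carries the same restriction: "Safety outcomes will be any serious adverse events and clinical events".

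Three other places bear on the point.

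- **Exclusion criteria.** The contraindications to the device include "scars, bruises, scratches or inflammation on the skin of the acupoints; allergic to electrodes".
- **TEAS group.** On exposure, "the patients in the TEAS group will receive 48 sessions of TEAS treatment (4 times weekly for 12 weeks"). On intensity, "patients asked to increase the stimulus intensity until local, rhythmic contractions of the muscle are obtained without producing pain". The software is described as logging the date, duration and acupoints of each stimulation; reactions are not mentioned.
- **Statistical analysis.** The safety set consists of those who had at least one TEAS session, and the safety analyses use that set.

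**The concern.** The article does more than leave adverse event recording to a fuller document. It defines the safety outcomes twice, in matching terms, and the word serious limits what counts. The device uses adhesive electrodes on the skin at a patient-set intensity, at home, four times a week for 12 weeks. The harms that the document itself guards against, namely skin problems, electrode allergy and pain, will mostly be non-serious, so the definition would pass over them.

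At stake is whether the trial can say how well patients tolerate the device, which matters for an add-on treatment meant for wide home use. A patient who stops because of irritation would appear in the listed outcomes only as fewer completed sessions, under TEAS adherence, with no reason attached. Serious and cardiovascular events up to week 52 in patients aged 18 to 65 are worth counting, but they say little about local reactions during the 12 treatment weeks.

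**Working it through.** **1. The outcome list against the recognised risks**

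| Risk | Where the article recognises it | Covered by a listed outcome? |
|---|---|---|
| Skin reaction at the acupoints | Exclusion criteria | Only if serious |
| Reaction to the electrodes | Exclusion criteria | Only if serious |
| Pain from stimulation | TEAS group (intensity instruction) | Only if serious |
| Death, myocardial infarction, stroke, cardiovascular hospitalisation | Outcomes | Yes, three time points |

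The secondary and tertiary outcomes (diastolic pressure, control rate, drug use, 12-item Short-Form, body mass index, waist, physical activity, adherence) do not fill the gap. The data and safety monitoring board is described as reviewing trial data every 6 months, with no statement of which events.

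**2. The plan's own denominator**

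From Sample size calculation: 14 communities per group, allowing for 10% community loss, gives 14 / 0.9 = 15.6, so 16. Forty patients per community, allowing for 20% patient loss, gives 40 / 0.8 = 50. Then 16 × 50 = 800 per group, which agrees with the article.

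**3. Size under an assumed rate**

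The documents give no rate of non-serious reactions. Assume 1% to 5% of TEAS patients.

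- All 800 patients: 800 × 0.01 = 8; 800 × 0.05 = 40.
- The 560 left after the planned losses: 560 × 0.01 = 5.6; 560 × 0.05 = 28.

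**4. Could the trial estimate such a rate?**

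The approximate 95% half-width is 1.96 × √(p(1 − p)/n), multiplied by √(design effect) to allow for clustering. The design effect is 1 + (m − 1) × 0.01. The value 0.01 is the article's intracluster correlation for its blood pressure calculation; using it for reactions is a further assumption.

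| n | Design effect | p = 1% | p = 5% |
|---|---|---|---|
| 800 | 1 (clustering ignored) | 0.7 points | 1.5 points |
| 800 | 1 + 49 × 0.01 = 1.49 | 0.7 × 1.22 ≈ 0.8 points | 1.5 × 1.22 ≈ 1.8 points |
| 560 | 1 + 39 × 0.01 = 1.39 | 0.8 × 1.18 ≈ 1.0 point | 1.8 × 1.18 ≈ 2.1 points |

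At 5% the estimate would be good in every row. At 1% it would be rough, but enough to show that reactions are uncommon. No extra patients are needed; only the outcome is missing.

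**5. Who is analysed**

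The Outcomes section promises safety results in both groups. The safety set in Statistical analysis requires at least one TEAS session. Usual-care patients are not given TEAS, so that set contains no control patients. Any added safety outcome inherits this conflict.

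**The case against.** The strongest reply is that limiting safety outcomes to serious events is a defensible pragmatic choice for a non-invasive add-on treatment, and that it leaves the primary analysis untouched. The effect on the primary analysis is indeed nil. The choice still falls short of an aim that names safety without qualification.

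A reader might infer that the safety aim cannot be answered at all. The documents do not support that. Any serious adverse event and four kinds of clinical event are collected at three time points in both groups, and a local reaction that met the definition of serious would count.

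A reader might also infer that ordinary adverse events will never be recorded, or that the device would be reported as free of safety signals. That goes too far as well. The article condenses a full protocol that is not shown, and the figure with the assessment schedule is not shown either. What can be said is that these events are not listed as outcomes.

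Two further objections stand in part. The contraindications, the face-to-face training and the instruction to stay short of pain are risk controls: they show awareness of the risk, not an expectation of frequent reactions. Symptomatic low blood pressure could be offered as another uncounted harm, but the article does not name it as an expected effect, and it does track office pressure and number of drugs, so the point does not rest on it.

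Finally, device reactions have no counterpart in an unblinded arm without a device. That limits comparison between groups, but a descriptive rate in the TEAS group remains useful.

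**Conclusion.** The point holds in a limited form. The listed safety outcomes omit non-serious device-related reactions, so the stated aim of evaluating safety is covered for serious harm and not for local tolerability. That follows from the text of the Abstract and the Outcomes section and needs no assumption.

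Its size does rest on an assumption: at 1% to 5% of patients, roughly 8 to 40 of 800 would be affected without counting, or about 6 to 28 of 560 after the planned losses. The true rate could lie outside this range. The primary result is unaffected. The change is worth making because it is cheap and closes a gap between the aim and the outcomes.

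**What to change.** 1. In Outcomes, and to match in the Abstract, add non-serious adverse events in both groups as a safety outcome. For the TEAS group add a short prespecified list of device- and skin-related events. Ask at the existing week 12 visit and report descriptively by severity and relatedness. Keep the serious and clinical events at weeks 12, 26 and 52 as they are.
2. In Statistical analysis, reconcile the safety set with the promise of results in both groups, so that usual-care patients are included.
3. Recruitment began on 18 November 2020, so some patients may already be past week 12. Ask them at their next scheduled visit and flag the answers as recall. If collection is no longer possible, narrow the safety aim to serious and major clinical events. Record the change as a dated amendment.
4. Outcome assessors are masked and their blinding is tested at week 12. Someone else should take the device questions, at week 12 and at any later visit, because the answers would reveal the allocation.

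The cost is one short form, one table and an unmasked person to ask the questions. There are two limits. A single question at week 12 relies on memory over up to 48 sessions, and open-label reporting will probably raise the count of mild events in the TEAS group. Both should be stated with the results. If the full protocol already collects these events, the change is only to list them as an outcome and correct the safety set.

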**Figure 3 F3:**
[figure not shown]
Schedule of enrolment, intervention and assessments. TEAS, transcutaneous electrical acupoint stimulation.

### Sample size calculation

The effective sample size (ESS) of 392 patients in each group is calculated for SBP on the basis of an alpha level of 0.05 (two sided), a beta level of 0.80, an expected between-group difference of 6 mm Hg,^19^ an SD of 10 mm Hg and a superiority margin of 4 mm Hg,^28^ if randomisation takes place at the individual level. With average 40 patients per community and an intracluster correlation of 0.01,^29^ the ESS should be multiplied by a design effect of 1.39, leading to 560 patients in 14 communities per group (1120 patients in 28 communities in total). As our experience suggests that up to 10% of the randomised communities and up to 20% of the recruited patients may drop out of the study, we aim to recruit 32 communities (16 per group) including 50 patients each, resulting in a target sample size of 1600 recruited patients in total (800 per group).

### Statistical analysis

A full analysis set, a per-protocol set and a safety set will be used in this trial. The full analysis set will consist of all randomised patients according to the intention-to-treat principle. The full analysis set will be the primary analysis, and all analyses will be conducted for this population if not otherwise stated. The per-protocol set will include those who complete all follow-ups on time and without major violations. Major violations include but are not limited to not ineligibility according to the inclusion and exclusion criteria, receiving medicines that affect blood pressure except antihypertensive drugs, or not completing ≤38 sessions TEAS (80% of prespecified 48 sessions). The per-protocol set will be the secondary analysis set and will be used for the sensitivity analyses for the primary outcome. All those who receive at least one session of TEAS will be defined as the safety set, which is used for the safety analyses.

Baseline characteristics will be summarised by groups. Continuous variables will be described using the mean (SD), or the median (IQR) if the normality assumption is violated. Categorical variables will be described using the frequency (percentage). The significance level of superiority test will be set at one-sided 0.025 for the primary outcome. The significance level will be set at two-sided 0.05 for secondary outcomes. All analyses will be carried out using SAS V.9.3.

The change from baseline in office SBP at week 12 will be analysed by a mixed-effect model using baseline value as a covariate, treatment group as a fixed effect, and community and interaction between community and treatment as random effects. Multiple imputation will be used for missing data.^30^ For the secondary and tertiary outcomes, continuous variables will be compared at all follow-up time points using a mixed-effect model with repeated measurement methods. If there is a normality violation in the continuous variables, a transformation will be performed before the test. Categorical variables will be compared using a generalised linear mixed-effect model. The consistency of treatment effects on the primary outcome will be explored in predefined subgroups, including sex, education and taking antihypertensive drugs or not and urban or rural community.

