## Methods

### Study design

This two-arm, open-label, cluster randomised controlled trial will be conducted at 32 community health service centres in China. The total trial period was 52 weeks, including 12 weeks of treatment and 40 weeks of follow-up. The study protocol (version number: 2.0; 13 June 2020) has been registered on Chinese clinical trial registry (No. ChiCTR2000039400). The protocol will be reported following the SPIRIT guideline.^20^
Figure 1 shows the flow diagram of the trial.

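### Two per-protocol exclusion rules are worded in reverse, and the set requires attendance to week 52 for a sensitivity analysis of a week-12 outcome

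*Protocol article*

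**What the plan says.** All the rules at issue are in the Statistical analysis section of the protocol article.

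- Entry to the set: "The per-protocol set will include those who complete all follow-ups on time and without major violations".
- Eligibility: "Major violations include but are not limited to not ineligibility according to the inclusion and exclusion criteria".
- Adherence: a further major violation is "not completing ≤38 sessions TEAS (80% of prespecified 48 sessions".
- Use: the per-protocol set is the secondary analysis set and "will be used for the sensitivity analyses for the primary outcome".

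Three other places fix the context. The TEAS group section plans "48 sessions of TEAS treatment (4 times weekly for 12 weeks". The Outcomes section defines the primary outcome as the "mean difference in the changes in office SBP from baseline to 12 weeks between TEAS and usual care groups", and says of the remaining efficacy outcomes: "All secondary outcomes and tertiary outcomes will be measured at weeks 12, 26 and 52". The Study design section says: "The total trial period was 52 weeks, including 12 weeks of treatment and 40 weeks of follow-up".

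The primary analysis is on the full analysis set, that is, all randomised patients, with multiple imputation for missing data.

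**The concern.** A per-protocol set should keep eligible patients who took the treatment as planned and were measured as planned for the outcome being analysed. Each part of that goes wrong here.

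First, the eligibility rule carries a surplus negative and so names eligible patients as violators. Second, the adherence rule combines a negative with a less-than-or-equal sign and so names the patients who met the target. Third, the attendance rule reaches 40 weeks past the primary endpoint, so a patient's place in a week-12 comparison depends on events after week 12.

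The per-protocol analysis is the only sensitivity analysis that the article names for the primary outcome. If its membership has to be interpreted at the analysis stage, part of its value as a pre-specified check is lost. The third point is one of substance. In an open-label trial, attendance at weeks 26 and 52 could depend on the arm and on perceived benefit, and selecting on it could distort the week-12 contrast. The article offers no figure for this, so it is a risk and not a demonstrated bias.

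**Working it through.** **Inputs.** Planned sessions: 4 per week for 12 weeks (TEAS group section). Threshold: 80%, printed as 38 sessions (Statistical analysis). Visits: weeks 12, 26 and 52 (Outcomes). Primary endpoint: week 12 (Outcomes).

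**Step 1: reproduce the plan's figure.** 4 × 12 = 48 sessions. 0.80 × 48 = 38.4, which rounds down to the printed 38. As percentages, 38/48 = 79.2% and 39/48 = 81.3%. The smallest whole number of sessions that reaches 80% is therefore 39.

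**Step 2: the adherence rule, literally and as repaired,** over 0 to 48 sessions:

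| Reading | Major violators | Patient with exactly 38 sessions |
|---|---|---|
| As printed (not completing ≤38) | 39 to 48 | kept |
| Delete the negative (completing ≤38) | 0 to 38 | excluded |
| Reverse the sign (not completing ≥38) | 0 to 37 | kept |
| Below 80% of 48 (fewer than 38.4) | 0 to 38 | excluded |

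The printed rule selects exactly the patients at 81.3% to 100% adherence. The two repairs differ only at 38 sessions. Deleting the negative agrees with the stated 80%; reversing the sign keeps a patient at 79.2%.

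**Step 3: the eligibility rule.** Taken literally, not being ineligible means being eligible, so every eligible patient is a violator. Applied together with Step 2, the printed rules would leave only ineligible patients with 0 to 38 sessions. Nobody could have intended that set.

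**Step 4: which arm.** Usual-care patients complete 0 sessions. Once the adherence rule is corrected to exclude 38 or fewer, 0 ≤ 38 would make every usual-care patient a violator unless the rule is limited to the TEAS group.

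**Step 5: attendance against endpoint.** The endpoint is at week 12 and the last visit at week 52; 52 − 12 = 40 weeks. Consider a TEAS patient with 48 sessions, an on-time week-12 reading and a missed or late visit at week 26 or 52. The primary outcome is complete, yet the patient fails the attendance rule. Nothing elsewhere in the article limits the required follow-ups to week 12.

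**Step 6: how many.** The sample size section allows for up to 20% of recruited patients dropping out but does not say when. No attrition between weeks 12 and 52 is given, so the loss cannot be calculated.

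**The case against.** The strongest reply is that the two reversed rules are language slips in a condensed article. The sentence itself gives the 80% target, and the TEAS group section says that patients with poor compliance will be prompted to finish the 48 sessions, so the direction is not in doubt. The literal rules cannot even be run sensibly. This stands. A reader might infer that the trial will analyse the wrong patients; the article does not support that, because it would require someone to apply a plainly unintended reading. What remains is the patient with exactly 38 sessions.

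A second reply is that complete and punctual follow-up is a strict but coherent trial-wide definition, not a contradiction. That is fair as far as it goes. It does not answer the mismatch with the one use that the article names, a week-12 outcome. Nor does the article say that this is the set's sole use, so the criticism applies to the week-12 analysis and not to any later analysis for which full follow-up might be relevant.

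A third reply concerns size. A reader might take the 20% dropout allowance as the share of patients lost to the attendance rule. The article does not support this: the allowance is an overall one and is not assigned to weeks 12 to 52.

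Finally, the primary result rests on the full analysis set. Nothing here alters its estimate, its test or the sample size. That also stands, and it limits the severity.

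**Conclusion.** The point holds as a should-fix. The article misstates the per-protocol set in three ways: the eligibility rule is reversed, the session rule is reversed, and attendance to week 52 is required for a week-12 sensitivity analysis. The first two are wording errors with evident intent, and their practical residue is how to classify one session count, 38 (79.2%). The third is a substantive mismatch that excludes patients with valid week-12 data because of later attendance; its size is unknown. The conclusion assumes that the required follow-ups include weeks 26 and 52, which is the natural reading of the Outcomes and Study design sections. The primary full-analysis-set result is unaffected.

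**What to change.** Before database lock, restate the definition as follows.

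- Major violations: ineligibility under the inclusion or exclusion criteria; use of medicines that affect blood pressure, other than antihypertensive drugs; or, in the TEAS group only, completing fewer than 80% of the 48 sessions, that is, 38 or fewer.
- The authors confirm explicitly that 38 sessions counts as non-adherent, since this is the one value on which the possible repairs differ.
- For the week-12 primary outcome, require only an on-time week-12 visit, and assess violations up to week 12.

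The cost is wording only. No additional data are needed: the TEAS software already records each session, and the week-12 visit is already scheduled.

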## Discussion

To our knowledge, this is the first cluster randomised trial to investigate the effectiveness and safety of the smart phone-based TEAS as adjunctive therapy for hypertension.

This study is a community-based cluster randomised trial. There are several advantages for this design. First, contamination is one of the common biases, but it can be alleviated by the cluster design because only the communities randomly assigned to the TEAS group will have access to the instrument. Furthermore, communities were chosen with adequate geographical separation from each other. Second, patients will be recruited from their homes or communities. Unlike hospital-based studies, which only include those who seek medical help, our design will overcome the traditionally low detection of hypertension.

The TEAS in this trial can be received through smart phone at home by the patients themselves. The majority of hypertension patients had to travel by taxi or use public transportation to attend physician visits and prescribe antihypertensive drugs. If the effectiveness of TEAS is verified, this non-pharmaceutical therapy will result in additional savings of cost and burden. The time, expense and lost wages are also identified as barriers for controlling blood pressure. The smart phone-based TEAS at home may contribute to improving treatment adherence. Furthermore, several patients sometimes forget to take medicine, especially when they are busy working or tripping. As we mentioned before, we could use the background of TEAS software to recognise patients with poor compliance real timely and remind them to complete treatment.

The mechanism of acupuncture to reduce blood pressure is still unclear. It was found that TEAS could decrease sympathetic nervous system activity and increase parasympathetic nervous system activity,^31^ which may contribute to reducing blood pressure. Moreover, TEAS was shown to have a vasodilator effect.^32^ Our animal experiments also indicated that mitogen-activated protein kinases and β-adrenergic receptors were involved in the mechanism of acupuncture’s amelioration of hypertension.^33 34^

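### The safety set admits only patients who received TEAS, so the usual care arm is left out of the safety analysis although its safety events are to be collected

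*Protocol article*

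**What the plan says.** The abstract of the protocol article gives the aim as to "evaluate the effectiveness and safety of the smart phone-based TEAS as adjunctive therapy for hypertension". Safety is therefore part of the stated objective.

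The Outcomes section defines the events: "Safety outcomes will be any serious adverse events and clinical events (death, myocardial infarction, stroke and cardiovascular-related hospitalisations"). They are to be assessed "at weeks 12, 26 and 52 in both groups".

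The Statistical analysis section then fixes the population: "All those who receive at least one session of TEAS will be defined as the safety set", and it assigns the safety analyses to that set. The same section makes the full analysis set, which contains every randomised patient, the default for any analysis that is not assigned to another set.

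On who receives the device, the TEAS group section says: "In addition to the usual care, the patients in the TEAS group will receive 48 sessions of TEAS treatment". The Randomisation and masking section gives every patient in a centre the treatment allocated to that centre. The Discussion adds that "only the communities randomly assigned to the TEAS group will have access to the instrument".

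**The concern.** Receiving at least one session is the only condition for entering the safety set. That is a usual definition of a treated population when every arm has a study treatment to start. Here the comparator is usual care alone, which has no session to count, so the condition removes the whole comparator.

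The events named as safety outcomes also occur in hypertensive patients who never use the device. A count of strokes or cardiovascular admissions over 52 weeks in TEAS patients alone can be neither attributed to TEAS nor dismissed as background. The randomised usual care arm supplies that background rate, and the written definition leaves it out of the analysis. A statistician who follows the text literally would report one arm; one who follows the Outcomes section would report two.

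**Working it through.** **1. Size of the arms (Sample size calculation section).** The only figure involved is the planned number per group, so I reproduce it first.

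- Inputs: two-sided alpha 0.05; power 0.80 (printed as the beta level); expected difference 6 mm Hg; superiority margin 4 mm Hg; SD 10 mm Hg.
- Patients per group before clustering: 2 × (1.960 + 0.842)² × 10² / (6 − 4)² ≈ 392.4, that is 392, or 393 if rounded up. The article gives 392.
- Design effect: 1 + (40 − 1) × 0.01 = 1.39. Then 392 × 1.39 = 544.9, and 544.9 / 40 = 13.6, so 14 centres of 40 = 560 per group. This agrees with the article.
- Dropout: 28 / 0.9 = 31.1, taken up to 32 centres; 40 / 0.8 = 50 patients per centre. 32 × 50 = 1600 in total and 16 × 50 = 800 per group. This agrees with the article.

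**2. Who can enter the safety set.**

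| Patients | Planned number | TEAS sessions by design | In the safety set as written |
|---|---|---|---|
| TEAS arm, at least one session | up to 800 | 1 to 48 | yes |
| TEAS arm, no session | not stated | 0 | no |
| Usual care arm | 800 | 0 | no |

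The set therefore holds up to 800 TEAS patients and 0 of 800 usual care patients. Dropout does not alter the second figure: with the 560 per group expected to remain, it is 0 of 560.

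**3. Does another rule bring the usual care arm back?** The default to the full analysis set would do so if it applied. It applies only where no other set is named, and for safety another set is named. No other section of the article adds usual care patients to the safety set.

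**4. Are the control data available?** Yes. The Outcomes section plans the same events at the same three time points in both groups. A safety set covering both arms could hold up to 800 + 800 = 1600 patients without any further data collection.

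**The case against.** The strongest reply is that this is a slip of drafting with a limited consequence. The Outcomes section shows that both groups are meant, and the session rule reads as a treated-patient rule written with only the TEAS arm in mind. Control events are to be recorded, every randomised patient is in the full analysis set, and a data and safety board is to review the trial data every 6 months. Safety is not the primary outcome, and the Discussion acknowledges that showing a benefit in clinical events would take a larger and longer trial. Nothing in the design, the sample size or the primary analysis depends on the definition.

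Most of this stands, and it limits the point. A reader might infer that the trial has no comparator for safety events, or that its safety aim cannot be met. The documents do not support that: the comparator is missing from one named set, and the data to restore it are planned.

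A reader might also infer that non-serious device effects, such as skin reactions, are neglected because "Safety outcomes will be any serious adverse events and clinical events" covers serious and clinical events only. That is a separate question of scope. The article contradicts itself nowhere on it, the assessment schedule figure is not shown, and a condensed article may leave the recording of such events to the full protocol.

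What does not stand is that the evident intention makes a correction unnecessary. Condensing a protocol can explain a missing detail. It does not explain an explicit definition that conflicts with the article's own outcome section.

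**Conclusion.** The definition of the safety set is wrong as written. It excludes the whole usual care arm (0 of 800 planned patients qualify), while safety events are to be assessed in both groups. Followed literally, it gives a single-arm tabulation, and no between-arm difference can be estimated within that set. TEAS-arm patients who never start are excluded as well; the article gives no estimate of their number.

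This rests on two assumptions: that the allocation is followed, so that no usual care patient obtains a session, and that recruitment reaches its target. The first decides whether any usual care patient could enter the set. The second affects only the size of the arm that is left out.

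The conclusion goes no further. The effectiveness analysis and its power are not affected, and a comparative safety analysis remains possible from data already planned.

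**What to change.** Before the database is locked and the allocation is disclosed to the statisticians, replace the safety set sentence with one that covers both arms. Either of these would agree with the Outcomes section:

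- all randomised patients, analysed by allocated group; or
- all randomised usual care patients, plus TEAS-arm patients with at least one session.

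The first is simpler and keeps the comparison as randomised. The second keeps the idea of a treated population, but it removes patients from one arm only, so the number with no session should be reported beside it. TEAS-arm patients with no session should not be moved into the usual care group: that would break the centre-level allocation, and neither option needs it.

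State also that event proportions will be compared between arms with allowance for clustering by centre. The generalised linear mixed model already planned for categorical outcomes can serve. If events are too few for it to be fitted, a comparison of centre-level proportions is a workable fallback. Estimates with confidence intervals are more useful here than tests, since the trial was not sized for these events.

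The cost is one sentence for the set and one for the comparison. Visits, data collection, sample size and the primary analysis are unchanged.
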